# Study protocol of a randomized controlled trial of fistula vs. graft arteriovenous vascular access in older adults with end-stage kidney disease on hemodialysis: the AV access trial

**DOI:** 10.1186/s12882-023-03086-5

**Published:** 2023-02-24

**Keywords:** Arteriovenous access, Fistula, Graft, Hemodialysis, Older adults

## Abstract

**Background:**

Treatment of end-stage kidney disease (ESKD) with hemodialysis requires surgical creation of an arteriovenous (AV) vascular access—fistula (AVF) or graft (AVG)—to avoid (or limit) the use of a central venous catheter (CVC). AVFs have long been considered the first-line vascular access option, with AVGs as second best. Recent studies have suggested that, in older adults, AVGs may be a better strategy than AVFs. Lacking evidence from well-powered randomized clinical trials, integration of these results into clinical decision making is challenging. The main objective of the AV Access Study is to compare, between the two types of AV access, clinical outcomes that are important to patients, physicians, and policy makers.

**Methods:**

This is a prospective, multicenter, randomized controlled trial in adults ≥ 60 years old receiving chronic hemodialysis via a CVC. Eligible participants must have co-existing cardiovascular disease, peripheral arterial disease, and/or diabetes mellitus; and vascular anatomy suitable for placement of either type of AV access. Participants are randomized, in a 1:1 ratio, to a strategy of AVG or AVF creation. An estimated 262 participants will be recruited across 7 healthcare systems, with average follow-up of 2 years. Questionnaires will be administered at baseline and semi-annually. The primary outcome is the rate of CVC-free days per 100 patient-days. The primary safety outcome is the cumulative incidence of vascular access (CVC or AV access)-related severe infections—defined as access infections that lead to hospitalization or death. Secondary outcomes include access-related healthcare costs and patients’ experiences with vascular access care between the two treatment groups.

**Discussion:**

In the absence of studies using robust and unbiased research methodology to address vascular access care for hemodialysis patients, clinical decisions are limited to inferences from observational studies. The goal of the AV Access Study is to generate evidence to optimize vascular access care, based on objective, age-specific criteria, while incorporating goals of care and patient preference for vascular access type in clinical decision-making.

**Trial registration:**

: This study is being conducted in accordance with the tenets of the Helsinki Declaration, and has been approved by the central institutional review board (IRB) of Wake Forest University Health Sciences (approval number: 00069593) and local IRB of each participating clinical center; and was registered on Nov 27, 2020, at ClinicalTrials.gov (NCT04646226).

**Supplementary information:**

The online version contains supplementary material available at 10.1186/s12882-023-03086-5.

## Background

There are currently about 600,000 U.S patients with end-stage kidney disease (ESKD) who are on chronic dialysis, and each year an additional 110,000 patients initiate dialysis [1]. About 90% of these patients receive hemodialysis (HD), and each individual is dependent on a vascular access as their “lifeline”, delivering blood to the extracorporeal circuit and dialysis machine [2]. Of the three types of vascular access for HD—arteriovenous (AV) fistula (AVF), AV graft (AVG), and central venous catheter (CVC)—CVCs are the least preferred choice, due to their association with frequent episodes of bacteremia and central vein stenosis [3–9]. Ideally, all patients with advanced chronic kidney disease would undergo timely pre-ESKD placement of an AVF or AVG, such that it would be ready for use when they initiate HD, and avoid CVC dependence. Unfortunately, approximately 82% of U.S. patients initiate HD with a CVC, either because they have not undergone pre-ESKD access surgery or because the access is not ready for use at the time of HD initiation [1]. This subset of patients remains CVC-dependent until a permanent access (AVF or AVG) can be placed and becomes suitable for cannulation. Moreover, if the initial AVF or AVG is abandoned, the patient again becomes CVC-dependent until a second AV access is placed and ready to use.

Until recently, the consensus guidelines on vascular access strongly preferred AVFs over AVGs, as in some populations AVFs have a longer secondary patency for dialysis and require less frequent surgical or percutaneous interventions to maintain their patency. On the other hand, a higher proportion of AVFs than AVGs are abandoned prior to their successful use, resulting in prolonged CVC-dependence. The superiority of AVFs over AVGs has been questioned, in particular for older (≥ 60 years) adults, who currently account for 60% of patients initiating chronic HD for treatment of ESKD [1]. Contemporary observational studies comprised of large cohorts of older adults have suggested that AVGs may confer similar or better patient outcomes than AVFs [10–12]. In an intention to treat analysis, AVGs had a higher secondary patency rate than AVFs in the first 18 months of access creation [13, 14]; shorter time to access cannulation; and lower rates of adjuvant procedures than AVFs, conferring faster transition to CVC-free HD [6, 15–17]. A meta-analysis of 13 studies concluded that older patients have a 50–65% higher risk of primary AVF failure and 80% higher risk of secondary AVF failure compared with younger patients [18].

### Rationale for the AV access study

Given the limitations of observational studies, there is a fundamental medical uncertainty about whether AVFs are truly superior to AVGs in older patients on HD. Given clinical outcome equipoise, there is a need for a definitive randomized controlled trial (RCT) to assess the relative merits of AVFs and AVGs in this subset of patients. A pilot RCT of AVG vs. AVF placement in older adults on maintenance HD with a CVC showed that enrollment and randomization to one of the two AV access surgeries is feasible [19, 20]. The AV Access Study RCT was designed as a multicenter trial to conclusively compare the effectiveness and safety of AVG vs. AVF in older adults receiving maintenance HD via CVC without a functional AV access. The overarching hypothesis is that AVGs will confer a higher rate of CVC-free days, fewer adjuvant procedures on the AV access, lower healthcare costs, and superior patient-reported outcomes compared with AVFs.

## Objectives

The *primary objective* of the AV Access study is to compare the relative effectiveness of AVFs and AVGs in maximizing CVC-free days.

### Rationale for the selection of CVC-free days as the metric of AV access intervention effectiveness

In clinical practice, the decision to establish an AV access revolves around the goal of removing the CVC in order to decrease patients’ risk of developing central venous stenosis and/or sepsis associated with use of CVCs. Between AVGs and AVFs, observational data suggest an imbalance in the rate of access outcomes that render patients CVC-free [9]. Generally, AVGs offer shorter time to maturation and successful cannulation—but might have shorter functional patency after successful use for HD. By contrast, AVFs have higher rates of primary failure; those that mature often require more interventions and longer times to maturation and successful cannulation—but might have longer functional span [9]. Once successful use for HD is established, AVFs require less frequent interventions than AVGs to maintain patency for HD. Therefore, AV access effectiveness in terms of CVC-free days encompasses pivotal, immediate and long-term, access events: rate of access maturation, time to access maturation and successful cannulation, partial or complete thrombosis, cannulation-precluding infection, and functional patency.

*Other objectives* of this study include comparing healthcare costs and patient-reported experiences between the two types of AV access approach, listed in Table 1.

**Table 1 Tab1:** Study objectives, outcomes and measures

Objectives	Construct	Specific Measure	Source	Timing
	Primary Effectiveness Outcome			
Compare AV Access intervention effectiveness	CVC-free days	Rate of CVC-free days per 100 patient-days	Chart review	M0-End
	**Safety outcome**			
Compare access-related safety events	Rate of vascular access (CVC or AV access)-related severe infections	Hospitalizations or death due to AV access-related infections Hospitalizations or death due CVC access-related infections	Chart review	M0-End
	**Secondary Outcomes of Healthcare Costs**			
Compare vascular access-related healthcare costs	Healthcare costs, from the insurer perspective	Costs associated with vascular access care (index AV access, new AV access, and/or CVC)	Chart review	M0-End
	**Tertiary Outcomes of Patient-Reported Experiences**			
Characterize patient-reported outcomes	Satisfaction with AV access	Short-Form Vascular Access Questionnaire	Patient	M0, M6, M12, M18 & M24
	Health-related quality of life	EuroQol 5-dimension 3-level	Patient	M0, M6, M12, M18 & M24
	Regret with AV access intervention	Decision Regret Scale	Patient	M6, M12 M18 & M24
	Preferences	Attitude Scale (Tradeoffs Present/Future Health)	Patient	M0, M6, M12 M18 & M24
	Concordance between access approach and patient-reported goals of care	SUPPORT questionnaire	Patient	M0, M6, M12, M18 & M24
	**Other Outcomes**			
Compare vascular access-related outcomes	AV access primary failure	Rate of AV access maturation failure	Chart review	M0-End
	Time to AV access cannulation	Successful AV access cannulation	Chart review	M0-End
	AV access patency	Duration of AV access patency (primary, assisted, cumulative)	Chart review	M0-End
	CVC-related infections	Incidence rate of CVC-related infections per 100 patient-days	Chart review	M0-End
	AV access infections	Incidence rate AV access infections requiring or not requiring hospitalization, per 100 patient-days	Chart review	M0-End
	Adjuvant procedures	Endovascular or surgical procedures on AV access	Chart review	M0-End
	AV access infection rate	Local or systemic infections related to index AV access infection (e.g., cellulitis)	Chart review	M0-End
	CVC-related infection rate	Local or systemic infections related to CVC	Chart review	M0-End
	Hospitalization rate	Date and cause of hospitalization	Chart review	M0-End
	Survival	Date and cause of death	Chart review	M0-End
Evaluate relationships between preoperative physical function and index AV access outcomes	Preoperative frailty and index AV access outcomes	Grip Strength Chair stand test Pepper Assessment Tool for Disability Clinical Frailty Scale Index AV access primary failure Time to successful cannulation of index AV access Rate of adjuvant procedures on index AV access	Patient, Physician & Chart review	M0-End
M denotes month; M0, baseline; M6, month 6 etc.				

## Methods

### Study design

This is a national, multicenter, individually-randomized, parallel-group controlled trial which targets enrollment of 262 elderly patients with ESKD with one or more coexisting medical conditions that puts the patient at higher risk of AVF maturation failure, i.e., cardiovascular disease, peripheral arterial disease and/or diabetes mellitus. Participants are randomized to surgical AVF creation vs. surgical AVG placement (Fig. 1).

**Fig. 1 Fig1:**
[figure not shown]
**Study Design Flow Diagram** *Assessment time points for AV patient-reported outcomes will be set from the date of index AV access surgery

The populated SPIRIT checklist for this study is provided as **Additional file 1.**

## Patient population

The study population is drawn from older adults, age 60 years and older, with ESKD receiving chronic HD via a CVC, who have been referred for AV access placement by their treating providers.

## Study setting

The study is conducted at seven national healthcare systems (**Additional file 2**). Enrollment and/or study-specific assessments take place at outpatient vascular access surgery clinics, outpatient nephrology clinics, outpatient or inpatient dialysis units, and inpatient nephrology or surgical services. All participating centers have established, large-volume nephrology and surgical practices that provide vascular access care for patients with ESKD.

## Eligibility criteria

These are listed in Table 2. Medical suitability for AV access surgery will be determined according to regional standard care for each patient. Anatomic and surgical suitability for AVF creation or AVG placement will be determined by the vascular access surgeon, according to usual care.

**Table 2 Tab2:** Eligibility criteria

Inclusion criteria
1. Are of age 60 years or older
2. Have ESKD
3. Receive in-center HD as treatment for ESKD
4. Have CVC as the vascular access used for HD at the time of referral for AV access creation
5. Were referred by patient’s treating medical providers for placement of AV access
6. Have at least one of the following comorbid conditions: cardiovascular disease, peripheral vascular disease, and/or diabetes mellitus
7. Receive care for ESKD at medical facilities whereby the research team will have access to medical information (inpatient medical chart, outpatient medical chart, dialysis medical chart, outpatient interventional nephrology or interventional radiology procedures) during the study
8. Were evaluated by vascular access surgery and have native vasculature deemed preoperatively to be suitable for surgical creation of either type of AV access (AVF or AVG) in an upper extremity in the opinion of the surgeon
9. Are scheduled or will be scheduled for AV access surgery in an upper extremity, based on the plans developed by treating medical providers
10. Provide informed consent for study participation (for candidates with adequate consent capacity based on Consent Capacity Assessment tool) or obtain informed consent for study participation from a Legally Authorized Representative (for candidates unable to consent based on Decision-Making Capacity Assessment tool)
**Exclusion Criteria**
1. Receive home HD as treatment for ESKD
2. Anticipate kidney transplant within 6 months
3. Anticipate conversion to peritoneal dialysis within 6 months
4. Anticipate conversion to home HD within 6 months
5. Participate in another medical study, which, in the opinion of the site principal investigator, conflicts with this study
6. Have AVF creation planned by means other than surgical intervention (e.g. AVF creation is planned through endovascular surgery)
7. A condition in which, in the opinion of the site PI renders the patient not a good candidate for study participation.
AV, arteriovenous; AVG, AV graft; AVF, AV fistula; CVC, central venous catheter; ESKD, end-stage kidney disease; HD, hemodialysis.

## Recruitment

The approach to participant recruitment consists of two steps, prescreening and screening. At prescreening, clinic appointments are reviewed weekly by the study coordinators at each clinical center. For each patient ≥ 60 years old, scheduled for an evaluation of AV access creation, ESKD status, vascular access and comorbidities are appraised through review of electronic medical records. Those who pass prescreening are considered potential study candidates who will be screened at the time of their clinical appointment with and evaluation by the vascular access surgery. Patients who, in the opinion of the surgical team, have vasculature suitable for AVF creation and AVG placement in the upper extremity, will be approached for study participation. Before informed consent is obtained, the protocol requires the assessment of consent capacity for all study candidates using the using the Decision-Making Capacity Assessment Tool, enclosed in **Additional file 3**. The informed consent from the eligible candidate is obtained in a face-to-face interview with the patient or a Legally Authorized Representative for those without consent capacity.

## Randomization

After informed consent is obtained, a member of the study team at each clinical center enacts the randomization through the centralized REDCap platform (Fig. 1). The randomization system is based on a block-permutation scheme with variable (two to four) block sizes, and assigns participants in a 1:1 ratio to AVG or AVF placement, stratified by (a) clinical center and (b) history of previous AV access surgery.

## Blinding

Due to the visible nature of the intervention, blinding of the treating providers and investigators is not possible. Although the study intervention is unmasked, the clinical outcomes collected in the study are informed by medical diagnoses judged by the treating providers, independent of the study.

## Interventions

The study intervention is surgical placement of an AV access in an upper extremity (referred to as index AV access), either an AVF or an AVG, according to randomized allocation. Both types of AV access surgery are considered standard care. The specific vasculature used for index AVF or index AVG is at the discretion of the treating surgical team. The sites will use Food and Drug Administration (FDA)-approved grafts, with most common material being expandable polytetrafluoroethylene (ePTFE) grafts. Scheduling of the index AV access surgery date will occur according to local practices.

### Adherence to allocated intervention of index AV access surgery

After informed consent is obtained, the randomization assignment (i.e., type of index AV access to be surgically created) will be relayed to the vascular surgery team through verbal and electronic mail communication. Surgical intervention adherence to the assigned, index AV access is monitored during the study. All events of index AV access surgery postponement, missed surgery, or cancellation, with or without rescheduling, will be recorded along with the reason for such events.

### New AV Access surgery after index AV access surgery

If, over the course of follow-up, the index AV access is abandoned after its creation, the plan for and choice of a subsequent, new AV access will be at the discretion of the local medical team. Participants who undergo surgery for creation of a new AV access will continue to be followed until an end-of-study event. New AV access surgery will be subject to data collection similar to that of the index AV access surgery. AV access cannulation and complications during follow-up will identify whether it corresponded to the index AV access or a new AV access.

## Outcomes and measurements

All the outcomes, summarized in Table 1, are measured from the date of randomization to end-of-study event (i.e., drop out event or end-of-study date).

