### Secondary, tertiary and other outcomes

The secondary outcome will compare vascular access-related healthcare costs; rates of AV access maturation; rates of AV access adjuvant procedures; rates of infectious and non-infectious vascular access (CVC or AV access) complications; and deaths. Event definitions for AV access outcomes and CVC outcomes, and cause of death categorization are listed in **Additional file 4**. Standard costs attributed to vascular access (index AV access, CVC, new AV access) adjuvant interventions and complications will be used to calculate cumulative access-related costs between the two groups (**Additional file 5**).

Tertiary outcomes consist of patient-reported outcomes. Patients’ satisfaction with their dialysis vascular access will be elicited with the Vascular Access Questionnaire [21] and the Decision Regret Scale [22]. Health-related quality of life will be assessed with the EuroQol 5-dimension 3-level [23]. Patient’s preferences between quality/quantity of life and future/present health will be assessed with the Attitude Scale [24] and SUPPORT questionnaire [25]. These instruments are described in **Additional file 6**.

Exploratory outcomes will evaluate for relationships between preoperative frailty measures and the rate of index AV access primary failure, time to successful AV access cannulation, and the rate of adjuvant procedures on index AV access.

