Pepper Assessment Tool for Disability		X ^#^					
Clinical Frailty Scale^§^		X ^#^					
EuroQol 5-dimension 3-level^€^		X ^#^		X	X	X	X
Vascular Access Questionnaire score^€^		X ^#^		X	X	X	X
Attitude Scale (Tradeoffs)^€^		X ^#^		X	X	X	X
SUPPORT questionnaire^€^		X ^#^		X	X	X	X
Decision Regret Scale^€^				X	X	X	X
Duplex ultrasound of AV access				X (monthly)			
Hospitalizations (length and cause)		X (monthly)					
CVC complications^¶^		X (monthly)					
CVC removal / reinsertion		X (monthly)					
Adjuvant endovascular interventions^‡^				X (monthly)			
Adjuvant surgical interventions^‡^				X (monthly)			
AV access complications^¶^				X (monthly)			
Successful cannulation				X (monthly)			
AV access maturation failure				X (monthly)			
New AV access creation				X (monthly)			
Type of vascular access used for HD		X (monthly)					
End-of-study event^¥^		X (monthly)					
Serious Adverse Events		X (monthly)					

*Electronic medical records review

^£^Data collection when preoperative duplex ultrasound vascular mapping was performed

^†^Obtained in-person

^‡^Pertaining to AV access (index or new AV access) or CVC. ^§^Instrument will be completed by the treating physician. ^¶^Infectious and non-infectious complications and treatment

^¥^End-of-study event represents a drop out event (withdrawal of consent, withdrawal from the study, transition to peritoneal dialysis, transition to home HD, transfer of care outside participating health system network, kidney transplantation and successful discontinuation of HD, death) or end-of-study date

^€^Questionnaire administration between study coordinator and participant may take place in-person or via telephone

^#^Baseline questionnaires will be completed before index AV access surgery date or within 10 working days from the date of informed consent, whichever comes first

AV denotes arteriovenous; CVC, central venous catheter; HD, hemodialysis; M, month. Assessment time points for follow-up questionnaires will be set from the date of randomization

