## Statistical methods

### Sample size calculation and power considerations for primary outcome

The sample size estimate is based on the primary hypothesis that, by the end of the study, the patients in the AVG group will have more CVC-free days than patients in AVF group. Based on our pilot study [19, 20, 30], the average rate for CVC-free days was 15/100 patient-days among study patients who underwent AVF placement; similar or higher rate of CVC-free days was reported in other studies [31–33]. For this study, sample size calculations are based on two-sided tests with 5% type 1 error rate and a conservative estimate of 25% drop-out rate. Assuming a Poisson distribution and an average follow-up of two years, we will have > 90% power to detect a minimum of 5% points increase in CVC-free days in the graft group with 131 patients per group. We also considered situations where overdispersion is present for CVC-free days. With a total sample of 262 and 15/100 patient-days in the fistula group, we will have 80% power to detect an effect size of 25% for a 5% inflation of variance. The power will be greater if the rate of CVC-free days is 20/100 patient-days or higher in the fistula group.

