### Analysis for secondary outcomes

Access-related healthcare costs analysis will be based on the intention-to-treat principle. The costs will include index access placement (AVF or AVG), procedures required to promote study AV access maturation (angioplasty or surgical revision), procedures to maintain study AV access patency for HD after successful use (angioplasty, thrombectomy, or surgical revision), surgery to place a new vascular access (AVF or AVG) if the study AV access failed or was abandoned, procedures to promote maturation and maintain patency of all subsequent accesses, procedures of CVC exchange due to catheter dysfunction or infection, and reimbursement associated with access-related hospitalizations. Similar to our previous work, we will use the reimbursement fees established by the Center of Medicare and Medicaid Services, per each corresponding year of study, for access-related hospitalizations and inpatient or outpatient services and procedures [34]. Per-patient access cost will include the cost of all access-related procedures and hospitalizations divided by the total number of years of follow-up for that patient. As in standard economic analysis, costs will be discounted at 3% annually. Log transformation will be used to better approximate normality. A general linear model will be used to test the difference on the log scale between the fistula and graft groups. The estimates will be back transformed to represent median costs on the original scale. We will also use a generalized linear model with Gamma distribution and a log link to compare the mean access-related cost between the two groups.

Other secondary outcomes include rates of AV access maturation, rates of AV access adjuvant procedures, and rates of infectious and non-infectious vascular access (CVC or AV access) complications. Poisson regression models will be used to test the difference between AVF and AVG groups. If we observe overdispersion, we will explore the negative binomial models. Deaths will be analyzed using Cox regression models.

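### Death is followed only until drop-out, so deaths after an exit alive go uncounted in the Cox comparison; vital status could be followed to the end-of-study date at little cost

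*Protocol article*

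**What the plan says.** Under Outcomes and measurements, the article sets one observation window for everything: "All the outcomes, summarized in Table 1, are measured from the date of randomization to end-of-study event (i.e., drop out event or end-of-study date".

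The footnote to Table 3 defines the end of that window. It begins "End-of-study event represents a drop out event (withdrawal of consent, withdrawal from the study, transition to peritoneal dialysis, transition to home HD, transfer of care" and continues "transfer of care outside participating health system network, kidney transplantation and successful discontinuation of HD, death) or end-of-study date". Apart from death and the end-of-study date, every item on this list is an exit alive.

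Death falls under the rule. Table 1 lists survival, measured as "Date and cause of death" from chart review, among Other Outcomes. The section on secondary, tertiary and other outcomes also counts death among the secondary comparisons: "rates of infectious and non-infectious vascular access (CVC or AV access) complications; and deaths". The analysis section says only "Deaths will be analyzed using Cox regression models". Nothing in the article provides for learning whether a participant is alive after an exit.

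**The concern.** Stopping at exit suits outcomes that need dialysis and access records, because those records are out of reach once a participant leaves the network or in-center HD. Vital status does not depend on them. A participant who transfers out at month 4 and dies at month 7 is analysed as alive and censored at month 4.

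This has two consequences:

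- Deaths are lost from an outcome with limited numbers.
- The Cox model takes each exit as unrelated to the later risk of death. That is open to doubt for some exits. Transplantation, discontinuation of HD and home therapies may select healthier people, while transfer or withdrawal may precede decline. This is a reasonable inference; the article does not state it.

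If such exits also differ by arm, the mortality hazard ratio is distorted. That possibility cannot be dismissed, because treating providers and investigators know the allocation.

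**Working it through.** **Inputs from the article.** N = 262 (131 per group); average follow-up of 2 years; "a conservative estimate of 25% drop-out rate". The text does not say whether that 25% includes deaths, and Table 3 lists death as a drop-out event, so 25% is used as the upper end for exits alive. The article gives no death rate, event count or power for death, so there is no stated figure to reproduce.

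**Assumptions.** Death hazard d = 0.10 to 0.20 per year. Exits alive of 10% to 25% by 2 years (in the absence of death) at a constant rate e and unrelated to risk, with 2 years of follow-up for everyone.

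**Step 1: exit rate.** e = −ln(1 − p)/2, which gives 0.0527 per year for p = 10% and 0.1438 for p = 25%.

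**Step 2: share of deaths lost.**

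- Proportion dying within 2 years under complete follow-up: F = 1 − exp(−2d)
- Proportion whose death is observed when follow-up stops at exit: O = d/(d + e) × [1 − exp(−2(d + e))]
- Share lost: 1 − O/F

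| Exits alive | d | F | O | Share lost | Deaths in 262: complete → observed |
|---|---|---|---|---|---|
| 10% | 0.10 | 0.1813 | 0.1723 | 4.9% | 47.5 → 45.2 |
| 10% | 0.20 | 0.3297 | 0.3140 | 4.8% | 86.4 → 82.3 |
| 25% | 0.10 | 0.1813 | 0.1583 | 12.7% | 47.5 → 41.5 |
| 25% | 0.20 | 0.3297 | 0.2892 | 12.3% | 86.4 → 75.8 |

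The loss is therefore about 5% to 13% of deaths: 2 to 4 deaths at 10% exits and 6 to 11 at 25%.

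**Step 3: precision.** By Schoenfeld's formula, power = Φ(√(D/4) × |ln HR| − 1.96), with D the number of deaths. For an assumed hazard ratio of 0.6 and 25% exits, power falls from 0.42 to 0.38 at d = 0.10 and from 0.66 to 0.60 at d = 0.20.

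**Step 4: when the hazard ratio is biased.** Exit removes person-time as well as deaths. If exit is unrelated to risk, observed deaths divided by observed person-years still equals d, so the ratio between arms is unchanged.

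A simulation of 200,000 participants took prognosis-related exits. The true hazard ratio was 1. Half the participants had a death hazard of 0.1 per year and half had two or three times that. About 20% exited in each arm. The hazard ratio was approximated by the ratio of death rates.

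| Exit pattern | Ratio, stopped at exit | Ratio, complete vital status |
|---|---|---|
| Same prognostic pattern in both arms | 1.01 and 1.01 | 1.00 and 1.01 |
| Healthier leave one arm, sicker leave the other | 0.95 and 0.93 | 1.00 and 1.01 |

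In the same-pattern case the absolute death rate still shifts: 0.150 against 0.148 per year (about 2%) and 0.197 against 0.191 (about 3%).

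**The case against.** **Death is a minor outcome here, and the loss is modest.** This stands. Death comes last among the secondary comparisons, survival sits under Other Outcomes in Table 1, and no power is claimed for it. Deaths before any other exit are counted. If the 25% drop-out includes deaths, the loss lies below the top of the range. Power for a hazard ratio of 0.6 is limited even with complete follow-up.

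**The listed exits need not depend on access type.** This also stands. Transplantation, peritoneal dialysis or home HD anticipated within 6 months are exclusions, which limits early exits of those kinds. Nothing in the article shows that exits differ by arm.

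**The Missing data section already covers informative censoring.** Only in part. It offers shared-parameter and pattern-mixture models, but its sensitivity analyses are aimed at the primary outcomes. A model also cannot recover dates of death that were never collected, and neither can a later analysis plan.

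**A reader might infer a large bias.** If 15% of deaths in one arm and 30% in the other followed an exit, comparing the counts retained gives 0.85/0.70 = 1.21. That is a ratio of death counts. It approximates a hazard ratio only if participants leave shortly before dying, and twice as often in one arm. With exit unrelated to risk, losing 30% of deaths would need about 55% of that arm to exit by 2 years (in the absence of death), well above the planned 25%, and the hazard ratio would still be 1.00. The documents do not support such a figure.

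**A reader might also say that the comparison is no longer intention-to-treat.** That goes too far. The follow-up rule moves no one out of the assigned group; the defect is incomplete follow-up.

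**Conclusion.** The concern holds as one of incomplete follow-up for death. It follows from a stated rule, not from a detail left to another document. Under constant hazards, with 10% to 25% exits alive and a death hazard of 0.10 to 0.20 per year (both assumed), about 5% to 13% of 2-year deaths are not counted even when exit is unrelated to risk. Absolute survival can shift if exits relate to prognosis. The between-arm hazard ratio is biased only if prognosis-related exit differs by arm, and the documents allow neither a direction nor a size to be fixed. The primary outcome is unaffected. This is a cheap improvement to a secondary outcome, not a threat to the trial's main conclusion.

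**What to change.** For the death outcome only:

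1. In Outcomes and measurements and in the Table 3 footnote, separate the end of access-outcome follow-up from the end of vital-status follow-up.
2. Ascertain vital status and date of death to the common end-of-study date for every randomized participant who has not withdrawn consent to it.
3. Run the Cox model by assigned group with administrative censoring at that date. Where status stays unknown, censor at the date last known alive.
4. Keep the present drop-out rule for all outcomes that need access records.

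The cost is a short amendment and a vital-status check at close-out. Coordinators already administer questionnaires by telephone, which helps in part. The check will be harder for out-of-network transfers, some statuses will stay unknown, and cause of death will often be unavailable after exit, so the gain is mainly in all-cause mortality. The article reports enrollment in progress and completion estimated for the end of 2026, which left room for the change.
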